### Outcome measures

Outcome measures are collected at baseline defined by 3 days after discharge from hospital, and 1, 3, 6 and 12 months post-surgery. These data are obtained by self-administered questionnaires mailed to the patients, except for the questionnaire for baseline data, as the first questionnaires are handed to the patients just before discharge. The patients are contacted by phone once by research assistants if questionnaires are not received by the researcher 7 days after scheduled date for answering.

It is recommended to use a disease-specific health status measure supplemented by a generic measure of health-related quality of life to fully assess outcomes after TKA [32]. A combination of the WOMAC Index and SF-36 is the most frequently used combination [4] and will be used in this trial. Self-efficacy will be measured by the General Self-Efficacy Scale.

All questionnaires are validated and available in a Danish version.

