### Secondary outcomes

Secondary analysis will assess the effect of telephone follow-up in the intervention group compared to the control group by change in pain and stiffness scores in WOMAC LK 3.1 Index, change in health-related quality of life measured by the Medical Outcomes Study Short Form (SF-36) [27], change in the General Self-Efficacy Scale score [28], and the number of acute visits to the orthopaedic outpatient clinic.

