### Randomization and blinding

Patients are randomized 1:1 to the intervention group or the control group respectively. The randomization is performed centrally by a web-based randomization program and in blocks unknown to the investigator and other subjects involved in the study. The randomization is executed just before discharge of the patients from hospital.

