### Intervention

The participants allocated to the intervention group receive telephone follow-up 4 and 14 days post discharge in addition to conventional treatment. A uniform structure of the consultations is based on key subjects for nursing status defined by the VIPS-model (the Swedish acronym for the concepts Well-being, Integrity, Prevention and Safety). The VIPS-model is a process-oriented documentation model developed to generate structured general information about the patient’s condition, needs, desires, problems and resources relevant for nursing to provide adequate nursing interventions and evaluation of the outcomes [30,31]. The nursing status is based on predefined key subjects identified as relevant to assess the health status in the course of disease [31]. The telephone follow-up consultations are structured and contain the following key subjects: communication, cognition/development, breathing/circulation, nutrition, elimination, sleep, pain/perception, skin/tissue, sexuality/reproduction, activity and psychosocial /spirituality/culture. The themes are supplemented with specific issues relevant to health status after TKA in regard to treatment and observation of the wound and the operated limb, management of painkillers, and ability to exercise as recommended. However, the course of the consultations may vary due to the individual needs of the patients.

All interventions are conducted by the researcher responsible for this trial. The adherence of the protocol for the intervention is assessed by audiotaping consultations executed the first Wednesday in each month. Subsequently the records are checked by an external research assistant to ensure compliance with the protocol.

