In non-pharmacological trials the care providers and the patients are frequently un-blinded [46]. The lack of blinding could affect the estimate of the treatment effect positively [47]. In this trial neither the patients nor the person conducting the consultations are blinded after the randomization, because it is impossible to hide whether the patients receive consultation or not. The participants who are assigned to receive a new treatment including extra follow-up may have favourable expectations, and those assigned to conventional treatment may be disappointed [48]. However, the patients have no previous experiences of the rehabilitation period after TKA and hereby no basis for comparison of any gain of the follow-up consultations with conventional treatment after being discharged following TKA. Furthermore, the control group has no knowledge of the content of the consultations, and contact between patients post discharge with opportunity to discuss benefits or disadvantages of follow-up consultations are unlikely. However, it cannot be excluded that the patients meet by chance at follow-up in the outpatient clinic.

Deviation from the protocol after randomization is expected, since some patients will withdraw, some may be unavailable at the times set for the consultations, and some may not return the questionnaires. Exclusion of the patients deviating from the protocol destroys the distribution of similar characteristics in the two groups and could influence the estimation of the effect of the intervention [49]. Intention to treat analysis will be performed including all randomized patients providing the least bias when comparing results between the two groups [50]. The drop-out rate can be expected to increase during the 12 months follow-up period and rapid response to unreturned questionnaires is executed by telephone calls to minimize the drop-out rate.

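### The baseline questionnaire is due 3 days after discharge, after open randomisation and one day before the first call, so change from it is not a clean measure of effect

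*Protocol article*

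**What the plan says.** All references are to the protocol article.

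- **Outcome measures:** "Outcome measures are collected at baseline defined by 3 days after discharge from hospital". Later questionnaires are mailed, but "the first questionnaires are handed to the patients just before discharge". Patients are telephoned once "if questionnaires are not received by the researcher 7 days after scheduled date for answering".
- **Randomization and blinding:** "The randomization is executed just before discharge of the patients from hospital".
- **Discussion:** "neither the patients nor the person conducting the consultations are blinded after the randomization". The same section accepts that patients given the extra follow-up may have favourable expectations and that "those assigned to conventional treatment may be disappointed".
- **Intervention:** patients in that group "receive telephone follow-up 4 and 14 days post discharge in addition to conventional treatment".
- **Secondary outcomes:** the groups are to be compared "by change in pain and stiffness scores in WOMAC LK 3.1 Index", and likewise by change in SF-36 and in general self-efficacy.
- **Outcome analysis:** within-group change in continuous data is tested by a paired t-test.

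The article names no WOMAC, SF-36 or self-efficacy score taken before randomisation or before surgery.

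**The concern.** A baseline is useful because allocation cannot have affected it. Here it can. Even a form filled in on its due date is completed about three days after randomisation, by patients who report their own outcomes and can know whether a nurse will telephone them. A form filled in late in the intervention group may also follow the first consultation.

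The protocol itself names the mechanism. If disappointed controls score worse on day 3, their later change looks larger. If intervention patients score better on day 3, through favourable expectations or a call already received, their later change looks smaller. Both routes shrink the between-group difference in change, so they would tend to hide a benefit. The exposed results are the secondary change outcomes and the paired tests. The primary outcome joins them if the 12-point improvement under Primary outcome is read as change from baseline.

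**Working it through.** **1. Timeline, in days after discharge**

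| Event | Day | Section |
|---|---|---|
| Randomisation | 0 (just before discharge) | Randomization and blinding |
| Baseline form due | 3 | Outcome measures |
| First call | 4 | Intervention |
| Reminder if form not received | 3 + 7 = 10 | Outcome measures |
| Second call | 14 | Intervention |

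The form is due 3 days after randomisation and 4 − 3 = 1 day before the first call. The reminder comes 10 − 4 = 6 days after a call made on schedule. The article gives no rule that the form must precede the call, and does not say how late forms are handled.

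**2. The plan's own figure**

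Sample size gives a difference of 12, SD 18, α = 5% and power 90%. Two-sided, n = 2 × [18 × (1.960 + 1.282) / 12]² = 47.3, so 48 per group, as stated. This point does not change the sample size. The inputs are used only for the illustration below.

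**3. Effect of a shifted baseline**

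Let the true follow-up difference be 12 points in favour of the intervention, and let allocation move the day-3 score by b points in the same direction.

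- Comparison of follow-up scores: estimate = 12, whatever b is.
- Comparison of change scores: estimate = 12 − b.

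The article gives no value for b. Assuming b = 2 to 4, the change-score estimate is 10 to 8.

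**4. What that would mean for power**

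Further assumptions: SD 18 at both times, correlation 0.5 between them, 48 per group. The SD of change is then 18 × √(2 × (1 − 0.5)) = 18, and the standard error of the difference is 18 × √(2/48) = 3.67. Power is Φ(estimate / 3.67 − 1.96).

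| b (assumed) | Estimate from change | Power |
|---|---|---|
| 0 | 12 | 90% |
| 2 | 10 | 78% |
| 4 | 8 | 59% |

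These figures use the WOMAC function inputs. They would apply to the primary outcome only if it were analysed as change.

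**The case against.** The strongest reply is that the primary comparison probably does not use this form. Primary outcome and Sample size describe a 12-point difference between groups, and the WOMAC section sets the 12 points against an expected 6-month mean of 32. That reads more naturally as a difference in follow-up scores, which is unaffected. This stands. The word improvement leaves the matter open, but a reader should not infer that the primary result is biased by a sixth to a third of its target (2/12 to 4/12).

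Other inferences also go further than the article allows:

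- *Every late form in the intervention group was filled in after treatment began.* The reminder depends on receipt. A form completed on day 3 and posted slowly is late but precedes the call.
- *A baseline-adjusted analysis is compromised.* Outcome analysis plans none.
- *Day-3 values are carried forward as outcomes.* The article does not say so. It could arise only for patients who return no later form.
- *Randomisation cannot be checked.* Data collection lists age, gender, body mass index, ASA group and co-morbidities from medical records.
- *The one-week SF-36 recall biases the comparison.* The window is the same in both arms.

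The Discussion also argues that patients have no earlier knee-replacement rehabilitation to compare with and that controls do not know what the calls contain. This may reduce the shift, but knowing that a nurse will or will not call needs neither. For punctual forms, knowledge of allocation is the only route, and its strength is unknown.

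**Conclusion.** The point holds, with limits. The form called baseline is a post-randomisation measurement that known allocation, or for some late forms the first call, can influence. As written, the plan exposes the secondary change outcomes and the within-group paired tests to this, and the primary outcome too if it means change from baseline. Between-group comparison of follow-up scores alone is not biased by it.

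The mechanisms the protocol names would tend to understate benefit. Their size cannot be derived from the article, nor can the number of forms completed after the first call. The 2 to 4 points are an assumption. Under it a change-score difference is wrong by the same amount, and the power figures rest in addition on SD 18 at both times and correlation 0.5.

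The matter is worth settling promptly, because a baseline not taken before randomisation cannot be recovered later. Under Results, enrolment had reached 50%, about 0.5 × 116 = 58 patients.

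**What to change.** 1. **Patients still to be enrolled.** Have the form that is already handed out at discharge completed and collected on the ward, after consent and before the web randomisation is run. Define that form as baseline.
2. **Whole trial.** Define the primary and secondary between-group comparisons on follow-up scores at 1, 3, 6 and 12 months, not on change from the day-3 form. State this in Primary outcome and Secondary outcomes, and describe the day-3 form as a post-randomisation measurement.
3. **Sensitivity analyses.** Record completion dates where available. Analyse by enrolment period, and also exclude day-3 forms completed on or after day 4, with the same cut-off in both arms.

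**Cost.** Step 1 reorders tasks that already occur around discharge, but the two halves of the trial will have baselines from different times and settings. Ward scores reflect limited activity. With discharge 2 to 4 days after surgery, a one-week SF-36 recall on the ward reaches 7 − 4 = 3 to 7 − 2 = 5 days before surgery, whereas the day-3 form falls 5 to 7 days after it. Step 2 may cost some precision. With SD 18 at both times, change scores have SD 18 × √(2 × (1 − 0.7)) = 13.9 at correlation 0.7, but 18 × √(2 × (1 − 0.3)) = 21.3 at correlation 0.3, so follow-up scores are the less precise choice only above 0.5. For step 3, the article does not say that completion dates are recorded, so they may be missing for patients already enrolled.

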**Method/design:**

The design is a randomized un-blinded parallel group clinical trial conducted at the Department of Orthopaedic Surgery, Gentofte Hospital, the Capital Region of Denmark. In total, 116 patients will be allocated by an external randomization program to 2 groups: an intervention group following usual treatment after discharge supplemented by a nurse managed structured follow-up consultation conducted by telephone 4 and 14 days after discharge from hospital and a control group following treatment as usual. The consultations are structured by key subjects relevant to assess the health status according to the VIPS-model (the Swedish acronym for the concepts Well-being, Integrity, Prevention and Safety). The content of the consultations can vary according to the patients´ individual situations and needs. All consultations are conducted by the researcher responsible for the trial.

The effect is measured 1, 3, 6 and 12 months post-surgery. The primary outcome is self-reported physical function measured by The Western Ontario and McMaster Universities Arthritis Index. Secondary outcomes are self-reported health-related quality of life, general self-efficacy and the number of acute visits to the orthopaedic outpatient clinic.

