All interventions in this trial are conducted by the first author, reflecting the practice of that specific nurse and representing a positive attitude to the intervention, which could influence the outcome positively. The performance of the intervention will not reflect the intervention in an everyday clinical practice, which is influenced by the skills and attitudes of a range of nurses and the intervention needs to be tested in every day nursing practice to enhance generalizability. Random checks by audiotaping the intervention sessions and documentation in case report forms, assess treatment adherence essential to be able to appraise the feasibility and reproducibility of the intervention in clinical practice [51].

The effect of follow-up consultations by telephone after TKA has not previously been studied. Patient satisfaction with care related to information and contact with health professionals during stay in hospital was positively correlated with self-perceived health status up to 12 months after total hip and knee arthroplasty [52,53], and a long term effect of telephone follow-up consultations after TKA cannot be excluded. Due to timing and content of the intervention the effect is expected to be strongest and with the stated clinical relevant difference in scores between groups in the early recovery period.

Selection of patients enrolled in a trial may lead to problems with generalizability if the selected population differs in important ways to the more general one [44]. The practical value of a trial is supported by enrolling patients with characteristics that reflect the range and distribution of patients observed in clinical practice for a particular problem [54]. To enhance generalizability, all patients admitted are consecutively enrolled in this trial if they meet the inclusion criteria and none of the exclusion criteria. However, the sample in this trial will only represent the group of patients with a short stay in hospital, which minimizes the time for health-related counselling and information, but also increases the possibility of a positive outcome of the study.

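### Self-reported outcome forms are returned to the researcher who makes every intervention call; if patients know or assume this, courtesy reporting could add to the bias from lack of blinding

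*Protocol article*

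**What the plan says.** The abstract of the protocol article states: "The primary outcome is self-reported physical function measured by The Western Ontario and McMaster Universities Arthritis Index". Under Outcome measures the collection method is postal: "These data are obtained by self-administered questionnaires mailed to the patients". The baseline form is the exception, being handed over before discharge. The same section says that research assistants make one reminder call "if questionnaires are not received by the researcher 7 days after scheduled date for answering". The recipient of the forms is therefore named, and is distinguished from the assistants within one sentence.

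The Intervention section says who makes the calls, "All interventions are conducted by the researcher responsible for this trial", and who gets them: "The participants allocated to the intervention group receive telephone follow-up 4 and 14 days post discharge in addition to conventional treatment".

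The Discussion is open about blinding: "In this trial neither the patients nor the person conducting the consultations are blinded after the randomization". It accepts the likely direction of the resulting bias: "The lack of blinding could affect the estimate of the treatment effect positively". It also describes the single caller, identified there as the first author, as "representing a positive attitude to the intervention, which could influence the outcome positively".

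**The concern.** Read together, these sections have intervention patients returning their scores to the nurse who telephoned to help them, while control patients return theirs to someone who has not telephoned. In an unblinded trial with a patient-reported primary outcome, the patient is the assessor. A patient who wishes to please or thank the caller could report somewhat less functional limitation (a lower WOMAC score) or better health and self-efficacy (higher SF-36 and General Self-Efficacy scores). Control patients have no such relationship with the recipient.

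At stake is the between-group comparison on the primary outcome and on the questionnaire-based secondary outcomes. Any shift of this kind would look the same as a benefit of the calls, and nothing under Outcome analysis could separate the two. Unlike the lack of blinding itself, which the Discussion rightly calls unavoidable, the choice of recipient can be changed.

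**Working it through.** This is a question of conduct, so the main check sets the sections side by side.

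**1. Is the recipient the caller?** The abstract and the Intervention section give all consultations to the researcher responsible for the trial. The section on recruitment uses the researcher for one role (daily screening, and informing patients when assistants are absent) and names assistants separately. Outcome measures does the same. The consistent reading is one person, though this is inferred from usage and not stated in a single sentence.

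**2. Do the calls come before the outcome forms?**
- Table 1 requires discharge within 4 days of surgery. The second call is 14 days after discharge, so it falls by about day 4 + 14 = 18 after surgery.
- The follow-up forms are due at 1, 3, 6 and 12 months after surgery. All four come after both calls.
- The baseline form is due 3 days after discharge and the first call is on day 4. Courtesy arising from a call cannot affect a baseline form completed on schedule, so the point concerns the follow-up forms only.

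**3. Does the relationship differ by arm?** Yes. Only the intervention arm is called. The researcher may have informed some patients of either arm before randomization, but that is trial information, not counselling, and it is not tied to allocation.

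**4. Does the article deal with this route?** The Discussion covers patients' expectations, contact between patients and the caller's attitude. It does not mention where the forms go. Elsewhere the article does use people outside the intervention: assistants inform patients and make reminders, and an external assistant checks the audiotapes.

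**5. Can a size be given?** The only relevant figures are those under Sample size, and they reproduce:
- n per group = 2 × [18 × (1.960 + 1.282) / 12]² = 47.3, rounded up to 48, as stated.
- Standard error of the difference = 18 × √(2/48) = 3.67 points. A difference of 1.96 × 3.67 = 7.2 points reaches two-sided p < 0.05.

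These give the scale on which any bias would be judged. They say nothing about how large the courtesy effect of this return route is, and no other figure in the document does.

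**6. How many forms could still be redirected?** Under Results, inclusion began in January 2013, half of the 116 patients were enrolled, and completion was expected at the end of 2013. No 12-month form was then due.
- Minimum outstanding: 58 patients not yet enrolled × 4 forms + 58 enrolled × 1 twelve-month form = 232 + 58 = 290.
- Maximum: 116 × 4 = 464.
- Each pack holds 26 WOMAC items (7 + 2 + 17) and 10 self-efficacy items, so at least 290 × 36 = 10,440 entries before SF-36 and the other patient-reported items.

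**The case against.** The strongest reply is that the point hangs on a subordinate clause whose purpose is to define when a reminder is triggered. Receipt by the researcher does not establish who opens, reads or codes a form, or what the envelope or cover letter tells the patient. Outcome analysis names the data-entry software but no person, and the Ethics section promises confidentiality and anonymity. A condensed article may well leave such logistics to the full protocol. This stands as a limit: the mechanism is conditional on patients knowing or assuming that the caller sees their answers. It does not remove the point, because the recipient is something the article states, not something it leaves out.

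The second reply is that patients know their allocation and self-report wherever the forms go, and that the article already concedes the resulting bias. This also stands in part. Only the increment due to the recipient is at issue, and self-completion by post with reminders by assistants already limits interviewer influence.

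Two stronger readings are tempting. A reader might assume a shift of a few points, set it against the standard error of 3.67, and quote an inflated false-positive rate as the cost of this arrangement. The document gives no basis for any such shift, and part of it would be ordinary unblinding bias that remains after the forms are redirected. A reader might also infer that seeing early answers lets the caller distort the outcome through the second call. A baseline form could be in hand by then, but no route from it to a biased follow-up score is shown, and the follow-up answers arrive after the last scheduled call.

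**Conclusion.** The point holds in conditional form. The article places receipt of the follow-up questionnaires with the person who makes all intervention calls and is acknowledged to view the intervention positively, and its discussion of bias does not cover this. If intervention patients know or assume that the caller sees their answers, courtesy reporting could add to the bias already conceded, in one arm and towards benefit, on the primary outcome and the questionnaire-based secondary outcomes. The size of that increment is unknown.

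The conclusion rests on two assumptions: that the researcher in Outcome measures is the one in Intervention, which the usage supports, and that patients are aware of the recipient, which the article leaves open. It does not show that the trial's result will be biased. It identifies an avoidable route that is worth closing while most follow-up forms are still to come.

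**What to change.** In Outcome measures, for all outstanding 1-, 3-, 6- and 12-month forms:
- have the forms returned to and entered by the existing research assistants, under a study number;
- tell both arms, in the same words in the cover letter, that the person making the calls will not see individual answers;
- keep individual outcome data from the researcher until the last 12-month form is in.

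No new staff role and no extra patient burden are needed, but the cost is real. Receipt and entry of some 290 to 464 packs move to the assistants. Patients already enrolled will have returned early forms under the old arrangement and will return later ones under the new. The change applies equally to both arms under 1:1 block randomization. Its date should be recorded so that forms returned before and after it can be told apart in the analysis.
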